### Sample Size Calculation

The minimum required sample size was calculated using the standard formula for comparing 2 independent means, as shown below:

$$N=\frac{{\left(Z_{\alpha }+Z_{\beta }\right)}^{2}\left(P_{1}\left(1-P_{1}\right)+P_{2}\left(1-P_{2}\right)\;\right)}{{\left(P2-P1\right)}^{2}}$$

$$Z_{\alpha }=1.64$$

α= Type I error at 5%

$$Z_{\beta }=0.84$$

β= Type II error at 20%

The following parameters were used for the sample size calculation:

Improved facial esthetic and balance in maxillary DO=94%Improved facial esthetic and balance in maxillary unilateral Le Fort 1 osteotomy=44% (estimated clinically significant difference=50%)Difference (P2−P1)=50%Minimum sample size N=2×(1.64+0.84)^2^ (0.94) (1‐0.94) + 0.44(1‐0.44)/(0.50)^2^=7 each in 2 groupsSample size=14, with 7 in each group

Using a 2-sided z test with *α*=.05 and power of 80%, assuming a success rate of 94% in the dentoalveolar transport distraction group and 44% in the unilateral Le Fort I advancement group, the required sample size is 7 per group (N=14). This includes a 50% absolute effect size and accounts for variability in response.

The 50% effect size estimate was based on the internal pilot data and clinical observations. However, we acknowledge the possibility of overestimation. A sensitivity analysis will also consider a 40% effect size, which would require a larger sample and will be addressed in future studies.

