### Postoperative Care

All patients will receive antibiotics, analgesics, chlorhexidine mouth rinses, and dietary instructions. Follow-up visits will be scheduled at 1 month, 3 months, 6 months, and 1 year postoperatively.

As this is a prospective observational study, treatment allocation is not randomized. Patients are assigned to either the dentoalveolar transport distraction group or the unilateral Le Fort I advancement group based on specific clinical indications determined by the treating maxillofacial surgeon. Criteria such as cleft morphology, cleft width, presence of adequate bone stock for distraction, soft tissue quality, and anticipated compliance with the distraction protocols are considered during group assignment. To minimize selection bias, all assessments are conducted using standardized protocols, and outcome evaluators are blinded to the intervention type. Additionally, baseline characteristics of both groups will be statistically compared to assess equivalency, and any confounders will be adjusted for during analysis using multivariate regression techniques.

To further minimize allocation bias inherent to the nonrandomized design, we will perform stratified enrollment based on cleft width and age groups. Additionally, a propensity score adjustment will be conducted in the final analysis to balance any observed confounders between groups.

Missing data may arise from loss to follow-up or incomplete clinical or radiographic records. These will be assessed for randomness using the Little missing completely at random test. If data are missing at random, multiple imputation using chained equations will be applied to minimize bias. Variables with >20% missing data will be excluded from the primary analysis but may be used in sensitivity analysis. Potential confounders, such as patient age, cleft width at baseline, and compliance with treatment protocols, will be identified a priori based on clinical relevance and literature review. These variables will be included in multivariate regression models (eg, linear regression for continuous outcomes such as gap width and logistic regression for binary outcomes such as successful closure) to adjust the primary effect estimates. Adjusted effect sizes and CIs will be reported alongside unadjusted comparisons.

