### Statistical Analysis

All data will be analyzed using RStudio (version 4.3.2; Posit, PBC). Continuous variables (eg, cleft width and bone segment stability score) will be tested for normality using the Shapiro-Wilk test. Depending on data distribution, between-group comparisons will be performed using either the unpaired *t* test (for normally distributed data) or the Mann-Whitney *U* test (for nonparametric data). Categorical outcomes, such as arch form classification (U-shaped, V-shaped, or asymmetrical) and wound healing grades (from the Landry wound healing scale), will be compared using the chi-square test or Fisher exact test, as appropriate.

Longitudinal outcomes (eg, segment stability across time points) will be analyzed using repeated measures ANOVA for normally distributed data or generalized estimating equations for nonparametric repeated measures. All outcome measures will be reported with 95% CIs, and *P*<.05 will be considered statistically significant. Missing data will be handled using multiple imputation, and any potential confounders, such as age or initial cleft width, will be adjusted for using multivariate regression analysis.

To assess the robustness of results, sensitivity analysis will be conducted by comparing results from multiple imputation with complete-case analysis and worst-case scenario imputation.

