## Results

As of June 2025, patient recruitment, which began in April 2023, is ongoing. Out of 14 intended participants, 12 (85%) have been enrolled (with 7 in the dentoalveolar transport distraction group and 5 in the unilateral Le Fort I advancement group). The enrolled cohort includes 8 male individuals and 4 female individuals, with a mean age of 16.8 (SD 3.9; range 10-23) years. The average cleft width among the participants was 1.5 (SD 0.34; range 1.0-2.1) cm.

Data collection is anticipated to conclude by December 2025, and the results are expected to be published in 2026.

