## Discussion

### Anticipated Findings

This prospective observational study compares 2 graftless surgical techniques—unilateral Le Fort I advancement and dentoalveolar transport distraction—for the management of large alveolar clefts. On the basis of prior evidence, we anticipate that dentoalveolar transport distraction may achieve more predictable closure of wide alveolar gaps due to its capability for simultaneous bone and soft tissue regeneration through gradual mechanical tension [8,9]. Unilateral Le Fort I advancement, while traditionally used for midfacial hypoplasia and skeletal advancement, may offer improved esthetic facial projection but may be limited by the extent of cleft closure, particularly in large defects [10]. This study will evaluate and compare the clinical, radiographic, and soft tissue healing outcomes of both interventions to identify their respective advantages.

Several studies have demonstrated the effectiveness of dentoalveolar transport distraction in achieving successful cleft closure, even in patients for whom conventional bone grafting had failed [8,9,12]. These techniques exploit the principle of DO, first introduced to the craniofacial skeleton by McCarthy et al [7] and later adapted to the alveolar ridge [8]. Similarly, Le Fort I osteotomy, first described for cleft-related maxillary retrusion, has shown good results in terms of facial profile improvement and occlusion correction [11]. However, few prospective studies have evaluated these 2 methods head-to-head in a controlled population with similar cleft widths, making direct clinical comparison difficult. This study aims to address this gap by applying standardized clinical and radiographic outcome measures across both groups.

The study’s strengths include its prospective design, structured follow-up, and the use of objective evaluation tools, including CBCT for gap measurements and standardized scales such as the Landry wound healing scale and the bone stability scale. By focusing on large clefts (≥1 cm) and excluding patients with bilateral defects or prior interventions, the study enhances internal validity. Limitations include the relatively small sample size, which may limit generalizability, and the nonrandom allocation of patients to treatment groups based on clinical feasibility. However, multivariate regression will be used to adjust for baseline differences, and standardized surgical and postoperative protocols will minimize procedural variability.

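### A single, undefined worst-case imputation need not be conservative for a two-group comparison; two opposite extremes should be run instead

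*Protocol article*

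**What the plan says.** The Statistical Analysis section makes multiple imputation the method for missing data and tests robustness by "comparing results from multiple imputation with complete-case analysis and worst-case scenario imputation". It does not state the value given to each group, nor a worst value for gap width or for the three arch-form classes.

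The surrounding text matters here:

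- The null hypothesis (Introduction) is no difference in either direction, and P "<.05 will be considered statistically significant".
- Categorical outcomes are compared by the "chi-square test or Fisher exact test, as appropriate". The Postoperative Care section also foresees "logistic regression for binary outcomes such as successful closure".
- The sample size is 7 per group, "assuming a success rate of 94% in the dentoalveolar transport distraction group and 44% in the unilateral Le Fort I advancement group". The Discussion anticipates that "dentoalveolar transport distraction may achieve more predictable closure of wide alveolar gaps".
- By June 2025, 12 patients had been enrolled, "with 7 in the dentoalveolar transport distraction group and 5 in the unilateral Le Fort I advancement group". Recruitment was continuing, data collection was due to end in December 2025, and the last visit is at 12 months.
- On missingness: "Variables with >20% missing data will be excluded from the primary analysis but may be used in sensitivity analysis".

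**The concern.** For one patient, a worst outcome is easy to name. For a difference between two groups it is not: scoring a missing patient as a failure narrows the difference if that patient is in the better group and widens it if the patient is in the poorer group. A check that fails every missing patient is therefore a stress test only in one of these two situations.

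The article expects distraction (A) to do better, and its enrollment counts suggest that the latest patients will be in B. In that situation the check would push toward the expected answer, and a difference could be described as robust without ever meeting the assumption that could overturn it. With about 7 patients per group, one or two of them can decide significance.

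**Working it through.** **Plan's own figure.** The article gives none for the imputation. Its group size, used below, follows from its formula: (1.64+0.84)² × [0.94×0.06 + 0.44×0.56] / 0.50² = 6.1504 × 0.3028 / 0.25 = 7.45, reported as 7.

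**Who could be missing.** If 7 per group is met, the patients still to come number 7−7 = 0 in A and 7−5 = 2 in B. A patient enrolled after June 2025 reaches 12 months after June 2026, beyond the stated end of data collection. Two of 14 is 14.3%, under the 20% limit, so if these are the only gaps the 12-month variable stays in the primary analysis and enters the robustness check.

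**Effect on a binary closure outcome.** Assume that two B patients are missing, none in A, and A is ahead. The success counts are illustrations. For 7/7 v 2/5, two-sided Fisher:

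- Complete case: 3 failures among 12, all in B: C(5,3)/C(12,3) = 10/220 = .045. The opposite tail, C(7,3)/220 = 35/220, is more probable and is not added.
- Both scored as failures, 7/7 v 2/7: 2 × C(7,5)/C(14,5) = 2 × 21/2002 = .021.
- Both scored as successes, 7/7 v 4/7: 2 × C(7,3)/C(14,3) = 2 × 35/364 = .19.

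The five complete-case tables in this setting that are significant in favor of A, and one that is not:

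| Observed A v B | Complete case | Missing B = failure | Missing B = success |
|---|---|---|---|
| 5/7 v 0/5 | .028 | .021 | .29 |
| 6/7 v 0/5 | .015 | .005 | .10 |
| 7/7 v 1/5 | .010 | .005 | .070 |
| 7/7 v 2/5 | .045 | .021 | .19 |
| 7/7 v 0/5 | 1/792 = .001 | 2/3432 = .0006 | .021 |
| 6/7 v 1/5 | .072 | .029 | .27 |

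Four of the five significant results survive the all-failure rule and are lost under the opposite one. The last row shows significance being created.

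**How general this is.** All tables with A ahead and one or two patients missing in B only were enumerated: 27 + 23 for 7 v 7 and 19 + 15 for 7 v 5, 84 in all. Scoring the missing as failures never raised P and never removed significance. It created significance in 0 of 27 and 1 of 23 tables (7 v 7, one and two missing), and in 2 of 19 and 3 of 15 (7 v 5).

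**Where the same rule can fail.**

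- One A patient missing: 6/6 v 2/7, P=.021, becomes 6/7 v 2/7, P=.10.
- One missing in each group, 7 v 5: 6/6 v 1/4, P=.033, becomes 6/7 v 1/5, P=.072.
- B ahead with one B patient missing: 1/7 v 5/6, P=.029, becomes 1/7 v 5/7, P=.10.

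**Gap width.** If the worst value is the preoperative width (cohort mean 1.5 cm) and m is the observed group B mean, two imputed patients raise the B mean by 2/7 × (1.5 − m). This is 0.43 cm at m = 0, which requires every observed B gap to be fully closed, and 2/7 × 1.0 = 0.29 cm at m = 0.5. So 0.43 cm is an upper limit.

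**The case against.** The strongest reply is that the article never says that every missing patient is failed. A directional rule (missing A fails, missing B succeeds) fits the wording equally well, and under it a result favoring A is weakened: with one B patient missing, 6/7 v 1/6, P=.029, becomes 6/7 v 2/7, P=.10. The definition of an imputation scenario is also commonly left to an analysis plan, which is not shown. This stands: the missing definition alone is no error. What remains is that the article commits to one extreme for a comparison without direction, and under either reading only one side is examined.

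A reader might infer that the check cannot fail, or that it is shown to be biased toward distraction. The documents do not support that. The rule is undefined, and even if it fails every missing patient, the result can be lost when A patients are missing or B is ahead. Missingness confined to B is likewise an assumption: enrollment dates by group are not given, any A patient operated on after December 2024 would also lack a 12-month visit by the end date, and no dropouts were recorded to June 2025.

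It can also be said that the planned complete-case comparison exposes the problem. It does so where significance is created (6/7 v 1/5: .072 against .029), but not in the four tables where complete-case and all-failure results agree and only the opposite extreme differs.

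Finally, binary closure appears only as a regression example, and the primary gap measure is radiographic. The Fisher figures therefore illustrate the direction and fragility of the check; they do not predict the main gap analysis.

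**Conclusion.** The point holds in a conditional form. One worst-case imputation, with no value stated per group, is not an adequate robustness check for a non-directional comparison of about 7 v 7. If it means failure for all, group A is ahead and only the last two group B patients lack 12-month data, it cannot weaken the result: P=.045 moves to .021, while the untested opposite assumption gives .19. This rests on recruitment reaching 7 per group, the December 2025 end date holding, no A patient being missing, and illustrative success counts. Creation of significance from a non-significant result is rare at 7 v 7 (one of 23 tables with two missing). The point is an inexpensive improvement to a sensitivity analysis; it does not show an error in the primary analysis.

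**What to change.** Replace the single worst-case run by two opposite extreme cases: missing A patients given the worst value and missing B patients the best, and the reverse. State the worst and best values for gap width in advance, for example the patient's own preoperative width and a gap of zero. Arch form has no class ranked as worst, so assign missing patients to each class in turn and report the range of results. Show both extremes beside the multiple-imputation and complete-case results, and do not call a difference robust on the basis of one extreme alone. A requirement that both extremes agree before any robustness claim is not needed; with 14 patients it would seldom be met once one or two are missing.

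The cost is a few lines of text and code, and robustness becomes harder to claim. If a directional rule was already intended, one sentence saying so removes the ambiguity, and the second extreme is then a small addition.

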## Results

As of June 2025, patient recruitment, which began in April 2023, is ongoing. Out of 14 intended participants, 12 (85%) have been enrolled (with 7 in the dentoalveolar transport distraction group and 5 in the unilateral Le Fort I advancement group). The enrolled cohort includes 8 male individuals and 4 female individuals, with a mean age of 16.8 (SD 3.9; range 10-23) years. The average cleft width among the participants was 1.5 (SD 0.34; range 1.0-2.1) cm.

Data collection is anticipated to conclude by December 2025, and the results are expected to be published in 2026.

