**Results:**

As of June 2025, institutional ethical clearance has been obtained and patient recruitment is ongoing. Recruitment began in April 2023, with 12 patients enrolled as of June 2025. Data collection is expected to be completed by December 2025, and results will be published in mid-2026.

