### Outcome Measures and Data Collection

Data collection will occur at predefined intervals: preoperatively; immediately after surgery; and at 1, 3, 6, and 12 months of follow-up.

The following outcome variables will be systematically evaluated in both groups:

Alveolar gap closure will be measured radiographically using cone beam computed tomography (CBCT) at each interval.Maxillary arch form will be classified (U-shaped, V-shaped, or asymmetrical) using dental models and occlusal views.Segment stability will be assessed clinically and via CBCT using the 5-point bone stability scale.Soft tissue healing will be evaluated by blinded assessors using the Landry wound healing scale.

All CBCT images will be anonymized and randomized. Two independent evaluators, blinded to group assignment, will perform measurements. If visible hardware reveals the treatment allocation, a second reviewer re-evaluated the image independently.

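### Data collection closes in December 2025, too early for the 12-month visit of any patient operated on after December 2024, and the missing-data rules do not provide for visits not yet due

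*Protocol article*

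**What the plan says.** - **Follow-up.** Outcome Measures and Data Collection schedules assessments before surgery, immediately after it, "and at 1, 3, 6, and 12 months of follow-up". Primary Outcome includes one year among the time points for alveolar gap closure and has arch form classified at every follow-up. Postoperative Care counts the visits from surgery.
- **Recruitment.** Results: "As of June 2025, patient recruitment, which began in April 2023, is ongoing". It continues: "Out of 14 intended participants, 12 (85%) have been enrolled". By group these are 7 distraction patients and 5 Le Fort I patients. Sample Size Calculation plans 7 per group.
- **End of study.** The Abstract states: "Data collection is expected to be completed by December 2025", with publication in mid-2026. Results agrees: "Data collection is anticipated to conclude by December 2025, and the results are expected to be published in 2026". Methods, Overview also ends the study in December 2025.
- **Missing data.** Postoperative Care foresees two causes: loss to follow-up and incomplete records. Missing data are to be "assessed for randomness using the Little missing completely at random test. If data are missing at random, multiple imputation" by chained equations follows. It adds: "Variables with >20% missing data will be excluded from the primary analysis", although such variables may enter sensitivity analyses. Statistical Analysis adds complete-case and worst-case comparisons.

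**The concern.** The article's own dates do not leave room for its last scheduled visit. A patient enrolled after the status report has about six months at most before data collection closes, yet the primary outcomes are to be measured at one year. The article does not acknowledge this.

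The gap comes from the calendar and is known in advance, but the missing-data text has no category for a visit that has not yet fallen due. Under the stated rules such visits would be handled like losses: imputed, set to worst case in a sensitivity analysis or, past a threshold, excluded with their variable. What is at stake is whether a one-year comparison of the two techniques can be delivered for all 14 patients, and whether its 12-month part is distorted by the closing date.

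**Working it through.** **Inputs.** Target 14, 7 per group (Sample Size Calculation). Enrolled by June 2025: 12, as 7 distraction and 5 Le Fort I (Results). Recruitment start: April 2023. End of data collection: December 2025. Last visit: 12 months after surgery. Exclusion threshold: more than 20% missing (Postoperative Care).

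**The plan's own figure.** 7 + 5 = 12, and 12/14 = 85.7%, printed as 85%. Two patients remain.

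**Latest usable surgery date.** December 2025 − 12 months = December 2024. For the 6-month visit it is December 2025 − 6 months = June 2025.

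**Patients 13 and 14.** Enrolled in June 2025 at the earliest, they reach 12 months in June 2026 at the earliest. By December 2025 they have at most about 6 months. Orthodontic preparation precedes surgery in both groups, so follow-up may be shorter still.

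**Certain shortfall at 12 months, if recruitment reaches 14.** 2/14 = 14.3%. If the 7-per-group target is met, both patients are in the Le Fort I group (7 − 5 = 2): 2/7 = 28.6% there, against 0/7 in the distraction group from these two patients.

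**The 20% rule.** Let k be the number of already enrolled patients operated on after December 2024. The share missing at 12 months is (2 + k)/14.

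| k | missing | share | above 20%? |
|---|---|---|---|
| 0 | 2/14 | 14.3% | no |
| 1 | 3/14 | 21.4% | yes |
| 2 | 4/14 | 28.6% | yes |
| 3 | 5/14 | 35.7% | yes |

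This treats each visit as a variable. If gap closure is instead one variable over the six listed time points, there are 14 × 6 = 84 values. Two missing 12-month values are then 2/84 = 2.4% and five are 5/84 = 6.0%, so the rule is not reached.

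**How likely is k ≥ 1?** Surgery dates are not given, so this is illustration only. Assume even accrual over 26 to 27 months, surgery at enrolment, and 5 to 6 months of 2025 elapsed.
- Expected k: from 5 × 12/27 = 2.2 to 6 × 12/26 = 2.8.
- Expected share missing: (2 + 2.2)/14 = 30% to (2 + 2.8)/14 = 34%.
- Chance of at least one: 1 − (1 − 5/27)^12 = 91% to 1 − (1 − 6/26)^12 = 96%.

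**When complete 12-month data could exist.** At 12/26 = 0.46 patients per month, two more take 2/0.46 = 4.3 months, to about October–November 2025. The last 12-month visit then falls in about October–November 2026 or later, after the mid-2026 publication date in the Abstract.

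**The Little test.** It tests missing completely at random. Not rejecting does not prove that condition, and rejecting does not rule out missing at random. It therefore cannot settle the condition on which imputation is made to depend.

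**The case against.** The strongest reply accepts the date conflict and disputes what follows from it. Most of that reply stands.

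- **The exclusion rule is not shown to fire.** The only documented shortfall is 14.3%, below the threshold. Crossing it needs a late surgery that the article does not report, and a reading of variables as single visits that the text does not state. Excluded variables may also still enter sensitivity analyses. This stands, so the consequence must be put conditionally.
- **Loss in one group only.** Allocation follows the surgeon's clinical indication, and 7 per group is a target. Any further late patients could be in either group. This stands: the 2/7 figure depends on the target being met.
- **Two imputation rules.** A reader might infer that Statistical Analysis, which mentions multiple imputation without a condition, contradicts Postoperative Care. It can equally be read as a summary of the fuller rule, so no contradiction is claimed.
- **Existing safeguards.** Complete-case and worst-case comparisons are planned, and generalized estimating equations, one of the longitudinal options, can use the available visits. Imputing visits missed for calendar reasons is not invalid in itself. This is true, but none of it separates not yet due from lost, and a worst-case value has no justification for a visit that was never due.
- **The date is an estimate.** All statements of December 2025 are worded as expectations. That makes the conflict cheap to repair, but it does not remove it.

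**Conclusion.** The schedule conflict holds on the document's own dates. Data collection that ends in December 2025 cannot give a 12-month visit to anyone operated on after December 2024. If recruitment reaches 14, at least two patients (14.3%) lack it; if the 7-per-group target is met, they are 28.6% of the Le Fort I group.

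The effect of the missing-data rules is conditional. With one or more further late surgeries, and visits counted as variables, at least 21.4% is missing and 12-month data leave the primary analysis. Otherwise visits not yet due are imputed or set to worst case as if lost. The 30–34% estimate rests on assumed even accrual and surgery at enrolment.

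Two rules are poorly fixed whatever the surgery dates: an exclusion threshold that could remove a primary outcome from the primary analysis, and a test of missing completely at random used to decide whether data are missing at random.

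A reader might infer that the 12-month outcome will certainly be dropped, or that the study will present short-term results as one-year results. The article supports neither. It gives no surgery dates, and it lists one year as one of several time points without naming it the sole primary one.

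**What to change.** 1. Set the end of data collection at the last patient's 12-month visit, and move the publication date with it.
2. If December 2025 is fixed, state that 12-month results cover only patients operated on by December 2024. Treat visits not yet due as administratively censored and keep them out of the worst-case imputation. Report how many such visits there are in each group, separately from losses.
3. Do not apply the 20% exclusion to primary outcome variables.
4. Do not make multiple imputation depend on the Little test. State the missing-at-random assumption and examine it through the sensitivity analyses.
5. Analyse all available visits with a method suited to each outcome type, and keep multiple imputation and complete-case analyses for comparison. No single model serves every outcome: an ordinary linear mixed model, for instance, does not fit the three-category arch form.

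**Cost.** Item 1 delays publication: at the observed pace the last 12-month visit falls in about October–November 2026 or later. Item 2 keeps the date but narrows the 12-month claim to fewer patients. Items 3 to 5 need changes of wording and no additional data.
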